### Measurements

In order to achieve the study goals and to answer the research questions, structured questionnaires and interview sheets, diaries, clinical and instrument-based examinations, and blood and stool tests will be used.

#### Medical history

Data will be gathered by means of an interview at SE. In addition to a basic clinical assessment, pre-existing internal and gynecological illnesses and general risk and protective factors such as body weight, alcohol consumption, nutritional behavior, level of activity, and number of pregnancies will be assessed.

#### Sociodemographic

Data will be collected at SE. The psychosocial and socioeconomic risk and protective factors such as living conditions, job situation, and income level will be assessed.

#### Medical radiation exposure

Data will be gathered by means of an interview at SE. The previous diagnostic and therapeutic X-ray exposure will be documented.

#### Study satisfaction questionnaire

This questionnaire will be handed out at V1 and V2. Questions are intended to capture the subject’s acceptance of the study, their satisfaction with the supervision, an evaluation of the physical activity and nutrition program, and their assessment of everyday practicality of the intervention program, where relevant.

#### Cardiovascular assessment

Within this examination at time points SE, V1, and V2, the patient’s medical history will be taken and a clinical examination with focus on the cardiovascular system will be performed. A resting electrocardiogram (ECG), pulmonary function testing, and blood pressure measurements are obligatory. Resting heart rate and blood pressure are to be recorded as measuring parameters.

#### Exercise testing/spiroergometry

Spiroergometry is an objective and well-known examination assessing cardiopulmonary exercise capacity. As the maximal oxygen uptake (VO_2_ max) and the aerobic and anaerobic respiratory capacity will be measured, the results enable a precise statement about the maximum cardiopulmonary capacity as well as aerobic and anaerobic capacity. The following target parameters (VO_2_ peak and O_2_ at ventilator anaerobic threshold (VAT)) [24] provide information about the fitness level at visits SE, V1, and V2.

#### Accelerometer

The AiperMotion 440/500 is a recognized physical activity meter, which objectively measures the scope of activity, as well as the steps and speed of movement [25–27]. The device is light (72 g) and has a three-dimensional digital acceleration sensor, which with an accuracy of 95%, classifies the level of movement into the categories “active,” “slow walk,” “fast walk,” and “jog.” The average level of activity is recorded as a physical activity level (PAL) value. The movement sensors will be distributed at five different time points in the first study year (SE–V2).

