**Methods:**

Therefore, we intend to enroll 60 BRCA1/2 mutation carriers in a pilot feasibility study (Lifestyle Intervention Study in Women with Hereditary Breast and Ovarian Cancer (LIBRE) pilot). This multi-center, prospective, controlled trial aims to randomize (1:1) participants into a (1) multi-factorial lifestyle intervention group (IG) versus (2) the control group with usual care (CG). The primary endpoint is feasibility and acceptance of a structured interdisciplinary lifestyle intervention program over 12 months (at least 70% of the patients to complete the 1-year intervention). Furthermore, the effects on physical fitness, BMI, quality of life, and stress coping capacity will be investigated.

During the first 3 months, women in the IG will receive structured, individualized and mainly supervised endurance training of ≥18 MET*h/week (MET = metabolic equivalent task) and personal nutritional counseling based on the Mediterranean diet. During the subsequent 9 months, the IG will receive monthly group training sessions and regular telephone contacts for motivation, whereas the CG will only receive usual care (one general counseling on healthy nutrition and benefits of regular physical activity on health status). At randomization and subsequent time points (3, 6, 12 months), cardiopulmonary fitness will be assessed by spiroergometry and nutritional and psychological status by validated questionnaires.

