**Fig. 1 Fig1:**
[figure not shown]
Design of the trial

**Table 1 Tab1:** Schedule of enrolment, interventions, and assessments

	Enrolment	Start	3 months	6 months	9 months	12 months	24 months	36 months	+12 months
Visit	SE	V0	V1	V1–6	V1–9	V2	V3	V4	Follow-up
Enrolment									
Eligibility screen	X								
Informed consent	X								
Randomisation	X								
Interventions									
Intervention group (I)	X	X	X	X	X	X	X	X	X
Control group (C)	X	X				X	X	X	X
Assessments									
Clinical baseline	C + I								
Clinical follow up						C + I	C + I	C + I	C + I
Spiroergometry	C + I		C + I			C + I			
Accelerometry	C + I		C + I	C + I	C + I	C + I			
Questionnaire “training” (IPAQ-L)		C + I	C + I	C + I	C + I	C + I	C + I	C + I	
Questionnaire “nutrition” (MEDAS, EPIC-FFQ)	C + I		C + I	I	I	C + I	C + I	C + I	
Lab	C + I		C + I			C + I	C + I	C + I	
Clinical examination	C + I		C + I			C + I	C + I	C + I	
Anthropometry	C + I		C + I			C + I	C + I	C + I	
Psychological questionnaires	C + I		C + I			C + I	C + I	C + I	

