### Statistical analysis and randomization

The sample size for the feasibility study is to be at least 60 women. For this study, the sample size was not determined based on statistical assumptions and tests, but on practical grounds that each center should recruit 20 participants. Primary and secondary endpoints will be analyzed descriptively. The primary endpoint will be determined according to the criteria shown in Table 4. Secondary endpoints will be described using absolute or relative frequencies, means with standard deviations, or medians with inter-quartile ranges as appropriate, for each of the study arms at the different time points. Measurements at months 3, 6, and 12 will be compared and tested against the baseline values using either parametric or non-parametric tests as appropriate. Randomization is to take place using envelopes, which will be deposited at the study center before the study begins. The group allocation (randomization) will be done centrally, using randomly permuted blocks of length 2–6. The randomization ratio is to be 1:1. We will use participating center and previous breast cancer as stratification factors. Each center will receive consecutively numbered, opaque envelopes, unique to them, split into two sets (one for previously diseased and one for healthy participants), containing the results. For each new participant, the principal investigator in the center will choose and open the first envelope from the diseased or healthy batch accordingly. As the study is not blinded, the allocation result will be concealed neither from participants nor from the principle investigators.

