One of the foreseen limitations of the trial will be selection bias for those patients being interested in lifestyle intervention and for those who will be randomized to usual care, especially for highly motivated participants. The latter patients may be disappointed on being assigned to the control arm and might either withdraw from the study or follow exercise instructions from the IG. These biases cannot be excluded in any lifestyle intervention trial. However, physical activity will be assessed using questionnaires and an accelerometer in both arms, and any cross-over of patients can be monitored. In addition, physical fitness will be objectively assessed by spiroergometry in both arms, which will also yield information on the long-term involvement of physical activity.

On the other hand, restraints for less motivated patients, e.g., due to professional obligations or as cares for children or other family members, may have an impact on adherence to supervised exercise sessions and everyday physical activities. In addition, a cross-over from CG to IG group for the Mediterranean dietary pattern cannot be excluded as previously outlined for physical activity. However, nutritional habits will also be assessed by questionnaire and BMI and body composition measured in both groups. Because of these problems in lifestyle intervention trials, it is a clear aim to avoid cross-over or bias of investigations by assuring that patients be treated identically regardless of the group assignment.

This LIBRE initiative (pilot and clinical study) will have the potential to reveal whether a structured lifestyle intervention program may prevent tumor incidence in BRCA mutation carriers. This will have to be compared with current risk-reducing strategies for women at risk, including prophylactic mastectomy, and could then be added to early detection programs. Furthermore, by following a structured exercise program and dietary changes, mutation carriers will attain an independent and self-governed role in cancer prevention and successfully reduce their stress levels [39]. By improving and optimizing the latter, we expect a preventive health effect not only on a somatic but also on the mental status of these patients.

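### Table 1 randomises at study entry, so as scheduled neither activity measure has a baseline secured before women know their arm

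*Protocol article*

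**What the plan says.** All references are to the protocol article.

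- **Randomisation.** Table 1 has a single mark in this row, in the SE column: "Randomisation X". V0, which Trial design defines as the start of the intervention, is a separate, later column.
- **Motion sensor.** Table 1 also places the first measurement at SE, in both arms: "Accelerometry C + I". The Accelerometer section says "The movement sensors will be distributed at five different time points in the first study year (SE–V2" and, on the output, "The average level of activity is recorded as a physical activity level (PAL) value".
- **IPAQ.** Table 1 leaves SE blank and has the first entry at V0. The Intervention group and Control group sections agree (V0 to V2). The IPAQ section under Measurements says it is collected from SE.
- **Blinding.** Statistical analysis and randomization states that "the allocation result will be concealed neither from participants nor from the principle investigators".
- **Use of the data.** The Control group section measures changes in activity behaviour with the IPAQ and the sensors. Study endpoints lists the IPAQ as a secondary endpoint and takes SE as the baseline. The statistical section tests months 3, 6 and 12 against baseline. The Discussion adds that "physical activity will be assessed using questionnaires and an accelerometer in both arms, and any cross-over of patients can be monitored".

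**The concern.** In an open trial a baseline is safe only if it is complete before the participant learns her arm. Activity is the behaviour most likely to respond to that news. The Discussion itself expects that some controls may be disappointed and may take up the intervention group's exercise.

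If the first sensor period or the first IPAQ falls after allocation, the reference value can already contain part of the reaction. Controls who become active at once would show too little later change, and so would intervention women who start early. Controls who are discouraged at first would show too much. Within-arm tests against baseline, which are the tests the plan describes, take this error over in full.

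The pilot is also meant to be the basis for the larger LIBRE trial, so its visit sequence may be carried forward.

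**Working it through.** **Step 1: counts.** Sensor time points in Table 1 within the first year are SE and months 3, 6, 9 and 12. That makes 5, which matches the Accelerometer section. The sample size is 3 centres × 20 = 60, as stated. With 1:1 allocation this gives 60 / 2 = 30 per arm. No power calculation underlies the 60.

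**Step 2: order of events against allocation at SE.**

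| Measure | First time point | Is a value before allocation secured? |
|---|---|---|
| Spiroergometry | SE | Implied: Table 2 excludes on VO2 max and on exercise capacity below 50 W, so the test must precede enrolment |
| Motion sensor | Handed out at SE | No: the average builds up after hand-out; no wear period or return before the envelope is stated |
| IPAQ (Table 1 and both arm descriptions) | V0 | No: V0 follows the visit of randomisation |
| IPAQ (its own section) | SE | Contradicts the row above; order within SE not stated |
| Other SE questionnaires | SE | Not stated; the Discussion has questionnaires answered in waiting times during the first visit |

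The Abstract does not settle the order either: "At randomization and subsequent time points (3, 6, 12 months), cardiopulmonary fitness will be assessed by spiroergometry". It places the first assessment at the randomisation time point without saying which comes first.

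The IPAQ asks about the last 7 days. The interval from SE to V0 is not given, so the days recalled at V0 may lie partly or wholly after allocation. In either case the answer is given by a woman who knows her arm.

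**Step 3: what a contaminated baseline could do.** This is an illustration only. The documents give no effect, no SD and no early reaction, so every value is an assumption in units of the SD of change. Take n = 30 controls and a two-sided paired normal test at 0.05. Let the true rise be d and the shift already present in the recorded baseline be b:

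- observed rise = d − b
- power = Φ((d − b)·√30 − 1.96) + Φ(−(d − b)·√30 − 1.96), with √30 = 5.477

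For d = 0.5 and b = 0.25: 0.25 × 5.477 = 1.369, then 1.369 − 1.96 = −0.591, and the power is 0.28.

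| Baseline shift b | d = 0.5: observed rise | d = 0.5: power | d = 0.3: observed rise | d = 0.3: power |
|---|---|---|---|---|
| −0.25 | 0.75 | 0.98 | 0.55 | 0.85 |
| −0.10 | 0.60 | 0.91 | 0.40 | 0.59 |
| 0 | 0.50 | 0.78 | 0.30 | 0.38 |
| +0.10 | 0.40 | 0.59 | 0.20 | 0.20 |
| +0.25 | 0.25 | 0.28 | 0.05 | 0.06 |

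A raised baseline hides a rise and a lowered one exaggerates it. The documents do not say which is more likely.

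**The case against.** The strongest reply is that Table 1 shows visits, not the order within a visit, and that a condensed article may leave wear period and envelope timing to the full protocol. No sentence says that the sensor is worn after allocation. Where the order within SE can be deduced, it runs the other way, because the eligibility limits put spiroergometry first. The Discussion also names spiroergometry in both arms, so one objective check keeps a baseline that precedes allocation. Cross-over can in part be judged from activity levels during follow-up, without any baseline. Accelerometry is not a listed secondary endpoint, and the endpoints are analysed descriptively.

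Much of this stands, and it limits the point to a baseline that is not secured rather than one shown to be contaminated. It does not remove the point. Randomisation at SE, sensor hand-out at SE and first IPAQ at V0 are fixed by the schedule. For the IPAQ, a listed secondary endpoint, Table 1 puts the first value at a visit after randomisation, while Study endpoints takes the baseline at SE. The Control group section speaks of changes, so follow-up levels alone are not the stated use.

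Two stronger readings are tempting and not supported:

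- A reader might infer that every baseline is taken after allocation. Spiroergometry argues against this. Some questionnaires would also hardly move on the day: the EPIC-FFQ covers the last year, and the LOT-R is described as measuring a personality variable.
- A reader might infer that cross-over will be under-detected. The direction is unknown, as the table of shifts shows.

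**Conclusion.** As scheduled, neither the motion sensor nor the IPAQ has a value secured before women know their arm, and the IPAQ time points contradict each other. Change-from-baseline activity data, and cross-over monitoring that relies on them, may be biased in either direction.

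The size cannot be taken from the documents. The power figures rest on assumed shifts and show only that modest ones would matter with about 30 women per arm. It would also be wrong to express the effect in MET*h/week: the sensor section reports a PAL value, the achieved MET*h/week is kept in training diaries, and controls receive none.

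The scope is secondary and cross-over data. The completion criteria in Table 4 use no baseline measurement. A reader might infer that women lost between SE and V0 distort the primary endpoint, but it is defined on randomised women. In a feasibility and acceptance trial, counting such losses is a legitimate choice.

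**What to change.** 1. State that the envelope is opened only after the SE questionnaires, a baseline IPAQ and the worn and returned SE sensor are on file. The simplest way is to move the randomisation mark in Table 1 from SE to V0, before the introductory lecture. The intervention marks that Table 1 now shows at SE for both arms would then need to be aligned.
2. Reconcile the first IPAQ time point (SE or V0) across Table 1, the two arm descriptions, the IPAQ section and Study endpoints, so that the value called baseline precedes allocation.

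The cost is small. V0 already exists, so no visit is added, and the envelope procedure stays as it is. Women learn their arm somewhat later. The interval from SE to V0, which is not stated now, must be long enough for the sensor to be worn and returned, and centres have less notice of the arm before arm-specific sessions begin.

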#### International Physical Activity Questionnaire

The IPAQ comprises five areas of activity, which are examined independently of each other [28]. The questionnaire is a simple instrument, which can be used to collect internationally comparable data for health-promoting physical activity over the last 7 days. The IPAQ is to be assessed at all study time points (SE–V2).

#### Examination of body composition

The examination of physical constitution comprises the documentation of anthropometric parameters such as height; body weight; waist, hip, and upper arm measurements; skin fold tests; and the bioelectric impedance analysis (BIA measurement) at the visits SE, V1, and V2, respectively. These measurements serve to record the percentage of body fat and the BMI and to determine level of lean body mass.

#### Blood tests

Within the context of the study, various blood values will be regularly determined (Table 3) in both the study arms at the time points (SE, V1, V2).

**Table 3 Tab3:** Blood measurements

Routine blood parameters measured in recruiting centers: • GPT (ALT) • Total cholesterol • HDL-cholesterol • LDL-cholesterol • Triglycerides • Glucose • Blood cell count • HbA1c	
Blood parameters measured in central or special laboratories: • Insulin • 25-OH-vitamin D • Selen • ß-carotine • Proencephalin A 119 D159 (Sphingotec GmbH) • Proneurotensin 1–117 (Sphingotec GmbH) • hsCRP (high sensitivity CRP) • Omega-3, 6, and 9 fatty acid content in the membrane of erythrocytes	

#### Stool samples

All subjects will provide stool samples (SE, V1, V2). A collective microbiome and metabolome analysis will be carried out at a later date.

#### EPIC-FFQ [29–31]

The questionnaire refers to food consumption during the last year and covers 148 food items. For each item, questions are asked concerning the average quantity consumed (pre-defined servings) and the frequency of consumption (1–6 times per day, week, month, or year). Color photos simplify the definition of serving sizes for food items, which are not consumed in normal household quantities. Furthermore, respondents are specifically asked about their use of cooking fats/oils, the frequency of consumption of sauces with meat and fish, the fat content of the milk they consume, the use of sugar and milk in coffee and tea, and the seasonal consumption of fresh fruit and vegetables. The data input and evaluation of the questionnaires is to be carried out via the study management system (SMS) for health research, which has been developed and is supervised by the Department of Epidemiology of the German Institute of Human Nutrition Potsdam-Rehbruecke (DIfE). The EPIC-FFQ will be conducted at SE, V1, and V2 in both study arms.

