## Methods

### Trial design

LIBRE-1 will be a multicenter, prospective, two-armed randomized (1:1) controlled clinical trial including *n* = 60 BRCA1 or 2 carriers. The aim of the study is to evaluate adherence to and acceptance of a structured, 1-year exercise program combined with a Mediterranean dietary pattern in BRCA mutation carriers. Additionally, physical fitness, body weight, quality of life, and stress coping capacity will be assessed. The study design is outlined in Fig. 1 and includes four visits (study entry (SE), start of intervention (V0), 3 months after start of intervention (V1), and 12 months after start of intervention (V2)). The schedule of enrollment, interventions, and assessments is shown in Table 1.

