*Nutrition*: Within the framework of the LIBRE-1 study, the nutrition intervention is based on the principles of a Mediterranean dietary pattern (MD). Furthermore, obese patients (BMI ≥ 35 kg/m^2^) will be instructed to limit their energy (kcal) intake. Nutrition intervention in the IG consists of an intensive phase of 3 months in line with the intensive physical exercise program. During this phase, bi-weekly nutrition education group courses will be held by dietitians. They include a cooking class and guided tour of a supermarket. Afterwards, nutrition courses will be reduced to monthly intervals. The main objective of the nutrition intervention is to provide practical nutritional training, which should enable the subjects to achieve a long-term change in their eating habits, replacing it with the MD. Eating habits will be recorded using validated questionnaires (EPIC-Food Frequency Questionnaire (FFQ) and Mediterranean Diet Adherence Screener (MEDAS)) at the time points SE, V1, and V2. The questionnaires are described below in the “Measurements” section.
*Psychological support*: Explicit psychological support is not planned. Psychological support of the IG will comprise solely of an explanation of the psychological data survey questionnaires given to the study participants. The participants will be informed that the objective of the lifestyle study is, among others, that the lifestyle change including regular physical activity and healthy eating should lead to an improvement in general life quality, stress reduction, and a more optimistic outlook on life. In order to verify this, the participants will receive questionnaires (Screening Scale for Chronic Stress (SSCS), Life of Orientation Test-Revised (LOT-R), European Organisation for Research and Treatment of Cancer (EORTC) Quality of Life Questionnaire Core 30 and Breast Cancer Module 23 (QLQ-C30/-BR23), and Assessment of physical activity and nutrition (BKAE)) at several time points (SE, V0, V1, V2). Advice on the psycho-oncological aspects of the LIBRE study will be given during the introduction lecture at the beginning of the study. The psychological advice given to the study participants will serve to inform the subjects of the significance and improvement of psycho-social lifestyles for the prevention of breast and ovarian cancer, as well as to promote compliance and recognize possible psychological impediments for participation in the study.

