### Study endpoints

The primary endpoint of the study is the number of randomized women who successfully complete the first 3 months of the intervention program and the monitoring/maintenance phase after 1 year. The study is considered feasible if at least 70% of the patients fulfill the criteria (see Table 4 for details).

**Table 4 Tab4:** Criteria for successful completion

Attendance of 70% of the planned lifestyle intervention events (training sessions and nutrition courses) within the first 3 months • Conduct of study visit after 1 year • No withdrawal of informed consent within 1 year • No new occurrence of any of the exclusion criteria during the first 3 months	

Secondary endpoints of the study include the measurements of quality of life (EORTC QLQ-C30-/BR23), stress coping (SSCS), optimism grade (LOT-R), body mass index (BMI), eating habits, nutrient and fat calorie intake (EPIC-FFQ), adherence to a Mediterranean diet (MEDAS), maximal oxygen intake (VO_2_ max), and physical activity (IPAQ). These measurements will be performed after 3, 6, and 12 months of intervention and compared to the baseline measurements at SE.

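### The EPIC-FFQ asks about the last year but is tested against baseline 3 months into the intervention, so the month-3 change in intake is biased toward no change

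*Protocol article*

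**What the plan says.** The EPIC-FFQ section of the protocol article sets the reference period: "The questionnaire refers to food consumption during the last year and covers 148 food items". The same section sets the timing: "The EPIC-FFQ will be conducted at SE, V1, and V2 in both study arms". Trial design places V1 at 3 months and V2 at 12 months after the start of intervention (V0), with study entry (SE) as a separate, earlier visit.

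Study endpoints lists eating habits and the intake of nutrients and fat calories, measured by the EPIC-FFQ, among the secondary endpoints. Of the secondary endpoints as a group it says: "These measurements will be performed after 3, 6, and 12 months of intervention and compared to the baseline measurements at SE". Statistical analysis and randomization adds: "Measurements at months 3, 6, and 12 will be compared and tested against the baseline values using either parametric or non-parametric tests as appropriate". The article states no different reference period for V1.

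V1 also closes the most intensive part of the dietary program: "Nutrition intervention in the IG consists of an intensive phase of 3 months in line with the intensive physical exercise program".

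**The concern.** The instrument, its recall period, the visit and the test are each stated, and they do not fit together. A woman who answers the V1 form as worded averages a few months on the program with a much longer stretch before it, and most of that stretch was already covered by her SE form. The month-3 test then compares two largely overlapping periods.

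Two misreadings could follow. A real change in diet during the intensive phase could look small or absent at V1. A larger change at V2 could then be credited to the later phase of monthly courses, although the recall window alone can produce that pattern. The Discussion says the LIBRE-1 results will be used to outline the program of the larger trial, so either misreading could carry forward.

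**Working it through.** The plan gives no figure for recall overlap or dilution, so there is none to reproduce. The inputs are the 12-month recall period (EPIC-FFQ section), the visit times (Trial design) and the comparison months 3, 6 and 12 (Study endpoints; Statistical analysis and randomization).

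**Share of the window before V0.** At month m (up to 12) this is (12 − m)/12.

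**Fraction of the full change that the form shows, with every recalled month weighted equally.**
- Diet changes fully at V0: m/12.
- Uptake is linear over the first 3 months (average one half, so 1.5 month-equivalents), then complete: (1.5 + m − 3)/12.
- Dilution is 1 divided by the fraction.

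| Month | Window before V0 | Full change at V0 | Linear uptake over 3 months |
|---|---|---|---|
| 3 | 9/12 = 75% | 3/12 = 25%, 4.0-fold | 1.5/12 = 12.5%, 8.0-fold |
| 6 | 6/12 = 50% | 6/12 = 50%, 2.0-fold | 4.5/12 = 37.5%, 2.7-fold |
| 12 | 0% | 12/12 = 100%, 1.0-fold | 10.5/12 = 87.5%, 1.14-fold |

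Month 6 matters only if the EPIC-FFQ is given then. The 1.14-fold at month 12 reflects the ramp-up itself; no pre-intervention month is in that window.

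**Overlap with the SE form.** The V1 window runs from 9 months before V0 to 3 months after it. The SE window ends at SE. The overlap is 9 months less the gap from SE to V0, which is not given. The V2 window starts at V0 and does not overlap the SE window.

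**Recent months remembered more strongly (assumption).** If each post-V0 month counts w times as much as an earlier one, the fraction shown at V1 with a full change at V0 is 3w/(3w + 9):
- w = 1.5: 4.5/13.5 = 33%, 3.0-fold
- w = 2: 6/15 = 40%, 2.5-fold
- w = 3: 9/18 = 50%, 2.0-fold
- w = 5: 15/24 = 62.5%, 1.6-fold

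The two departures pull in opposite directions. Linear uptake with w = 3 gives 1.5 × 3/18 = 25%, which is 4.0-fold again.

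**Growth without change.** If diet changes fully at V0 and then stays constant, the form shows 25% of the change at V1 and 100% at V2. The reported change quadruples while true intake after V0 does not move.

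**The case against.** The strongest objection is that the size depends on recall behavior nobody observes. This stands. Fourfold is the result of one set of assumptions. A reader might infer that no more than a quarter of the change can be seen at V1, but the documents do not support such a ceiling: with recency weights of 1.5 to 3, a third to a half is visible.

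A reader might also infer a collapse in power to detect a difference between arms. The article plans no between-arm test. It calls the analysis descriptive, states tests only against baseline, and gives no effect size or SD. Nor does a fourfold smaller mean imply a fourfold smaller standardized change. Under faithful averaging the true between-woman variation in change shrinks too, and only measurement error keeps its size. If error is half of the change-score variance (assumption), the standardized change falls to 0.25/√(0.0625 × 0.5 + 0.5) = 0.34, or 2.9-fold. If error is one fifth, it falls to 0.25/√(0.0625 × 0.8 + 0.2) = 0.50, or 2.0-fold.

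Third, a reader of Table 1 might extend the point to months 6 and 9. The table has one combined row for MEDAS and EPIC-FFQ, marked for the intervention group at those months, and does not say which form is used. The text sections place the EPIC-FFQ at SE, V1 and V2 only, and no comparison with baseline is planned at month 9. So month 6 is conditional and month 9 drops out.

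Fourth, diet at V1 does not rest on the EPIC-FFQ alone. MEDAS is given then in both arms, and blood markers such as beta-carotene and erythrocyte fatty acids are measured. This stands and limits the damage, but it does not repair the EPIC-FFQ test.

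Finally, the article is condensed and the V1 form is not shown, so a changed instruction cannot be excluded. The article nevertheless states the last-year reference and the V1 administration together, without exception.

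**Conclusion.** The mismatch is real and follows from the article's own statements. As worded, about three quarters of the V1 recall window precedes the intervention, and the planned month-3 change in EPIC-FFQ intake is biased toward no change. The dilution is fourfold with an immediate full change and true 12-month averaging. It is roughly two- to eightfold across gradual uptake and recency weights up to three, and milder still if recent months dominate recall more than that. Growth from V1 to V2 on this instrument cannot be read as growth in dietary change.

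The scope is narrow: one visit, possibly two, of one descriptively analyzed secondary endpoint. The SE-to-V2 comparison is sound. The primary feasibility endpoint does not use the questionnaire's content and is untouched. The point deserves correction because the fix costs almost nothing and prevents a misleading result at the end of the intensive phase.

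**What to change.** In Study endpoints and in Statistical analysis and randomization, define the EPIC-FFQ endpoint as SE versus V2 only. State that EPIC-FFQ change will not be tested or interpreted at month 3, or at month 6 if the form is given then. Name MEDAS as the 3-month dietary endpoint, supported by the diet-related blood markers already measured at SE, V1 and V2. No new data collection is needed.

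The cost is that there is no 3-month estimate of nutrient intake. MEDAS also has limits: the article does not state its recall period, and its German version is still to be validated within this pilot.

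Printing a 3-month reference period on the V1 form is not a clean alternative. Set against a last-year form at SE, it would mix reference periods and bring in seasonal differences in intake; the EPIC-FFQ section itself notes that the form asks about seasonal fruit and vegetables.
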